## Abstract

**Introduction:**

Anastomotic leak is a major complication after anterior resection for rectal cancer, with reported rates of 10–15%. Recent evidence implicates the gut microbiome, where specific bacteria colonise the anastomotic site and secrete collagenase that weakens healing tissue. Preclinical studies demonstrate that tranexamic acid can inhibit this process when delivered rectally into the bowel lumen. This protocol outlines a feasibility trial of rectally administered tranexamic acid delivered via rectal catheter to the anastomotic site after anterior resection, accompanied by embedded microbiome and qualitative substudies.

**Methods and analysis:**

This is an open-label, single-centre, randomised controlled feasibility trial. 45 patients undergoing anterior resection for rectal or sigmoid cancer will be randomised 2:1 to receive tranexamic acid or sterile water, administered intraoperatively and on postoperative days 1–3 via a rectal catheter. Feasibility outcomes include assessment of recruitment, intervention adherence, protocol compliance and safety. Exploratory clinical outcomes include anastomotic leak and other postoperative complications. A mandatory microbiome substudy will characterise changes in microbial composition and bacterial collagenase activity, providing mechanistic insight into treatment response. An optional qualitative substudy will explore acceptability of the intervention from the perspectives of patients and healthcare professionals.

**Ethics and dissemination:**

The protocol was approved by the North West Liverpool Central Research Ethics Committee and the Medicines and Healthcare products Regulatory Agency on 30 October 2024 (24/NW/0254). Recruitment commenced on 7 January 2025 following receipt of site-specific approvals. Feasibility, mechanistic and qualitative findings will be disseminated through peer-reviewed publications, academic conferences and stakeholder engagement activities. The results will inform progression to a definitive phase III trial and shape key elements of study design.

**Trial registration number:**

ISRCTN13727659.

STRENGTHS AND LIMITATIONS OF THIS STUDYEvaluates a novel, biologically plausible intervention with strong preclinical rationale, repurposing a widely used drug that has an established safety profile.Directly addresses key uncertainties of feasibility, safety and acceptability of rectal tranexamic acid delivered via rectal catheter.Incorporates embedded microbiome and qualitative substudies, providing both mechanistic insight and patient and clinician perspectives to inform future trial design.Given the limited sample size, the study is neither intended nor sufficiently powered to detect differences in anastomotic leak rates.

## Introduction

 In the UK, approximately 30 000 patients undergo surgery for colorectal cancer every year.^1^ Surgical management typically involves resection of the diseased bowel segment and restoration of gastrointestinal continuity by anastomosis. While potentially curative, this approach carries the risk of serious complications, the most significant being anastomotic leak. Anastomotic leak occurs when the anastomosis fails to heal adequately, resulting in leakage of intestinal contents into the abdominal cavity.^2^

The consequences of anastomotic leak can be severe. Patients may develop intra-abdominal abscesses, faecal peritonitis, multiorgan failure or death. Even when not fatal, leaks are associated with prolonged hospitalisation, increased morbidity and significant healthcare costs.^3–5^ Despite adherence to technical principles such as constructing a tension-free, well-perfused anastomosis, leak rates remain high. Following anterior resection, leak rates of 10–15% are reported, which are higher than for right sided resections.^6
7^

Increasing evidence suggests the gut microbiome may play a causal role in anastomotic leak. Certain commensal organisms, including *Enterococcus faecalis* and *Pseudomonas aeruginosa*, can colonise the anastomotic site and secrete collagen-degrading enzymes that weaken the structural integrity of healing tissue.^8^ Targeted modulation of the microbiome may therefore represent a novel strategy to prevent anastomotic leak.^9^

Tranexamic acid is a widely used antifibrinolytic agent that has been shown in preclinical studies to reduce bacterial collagenase production. Collagenase-producing bacteria exploit the host fibrinolytic system by activating plasminogen present within local anastomotic tissues, which upregulates collagenase activity and accelerates collagen breakdown.^10^ Tranexamic acid inhibits this pathway and reduces bacterial mediated collagen degradation in vitro and anastomotic leak in animal models.^11^

To achieve these rectal microbiome effects, local delivery of tranexamic acid into the bowel lumen is required. In patients undergoing anterior resection, where the anastomosis is in the rectum, this can be achieved using a rectal catheter. However, rectal administration of tranexamic acid has not yet been evaluated in humans. Before a definitive randomised controlled trial can be undertaken, it is necessary to establish whether this intervention is safe, feasible and acceptable, and to determine whether recruitment, intervention and follow-up processes for such a trial can be successfully delivered.

## Aims and objectives

The aim of this study is to assess the feasibility, acceptability and safety of rectally administered tranexamic acid and to determine whether a definitive randomised controlled trial can be undertaken to investigate the role of tranexamic acid in preventing anastomotic leak.

Objectives of the study include:

To identify participant, healthcare worker and logistical barriers to recruitment.To estimate realistic site-level recruitment rates.To assess participant and healthcare worker compliance to the intervention and trial processes.To obtain preliminary safety and efficacy data on rectally administered tranexamic acid.To evaluate the feasibility of conducting a phase III randomised controlled trial.

## Methods

### Study design

This study is a single-centre, parallel-group, randomised controlled feasibility trial evaluating rectally administered tranexamic acid to prevent anastomotic leak following anterior resection for rectal or sigmoid cancer (figure 1). 45 participants will be randomised in a 2:1 ratio to receive either tranexamic acid (1000 mg/50 mL) or sterile water (50 mL), administered intraoperatively and on postoperative days 1–3 via a rectal catheter positioned at the anastomosis. All participants will be followed up for 90 days after surgery.

**Figure 1 F1:**
[figure not shown]
Study flow chart. Flow of participants through the feasibility trial. The diagram shows key stages including recruitment, randomisation, delivery of allocated intervention, follow-up, and involvement in embedded microbiome and qualitative sub-studies. TXA, tranexamic acid; POD, post-operative day; RCT, randomised controlled trial; TXA, tranexamic acid.

The trial incorporates two embedded substudies: (1) a mandatory microbiome substudy to provide mechanistic insight into treatment response, and (2) an optional qualitative substudy to explore acceptability of the intervention and trial processes.

### Trial setting

The trial will be conducted at St James’s University Hospital, Leeds Teaching Hospitals NHS Trust, UK. This tertiary referral centre performs approximately 80–100 anterior resections annually and has established infrastructure for colorectal surgical research. Recruitment commenced on 7 January 2025, with study completion anticipated on 1 January 2027

### Trial participants

To be considered eligible for the study, patients must satisfy all of the following inclusion criteria:

Aged ≥18 years.Able to provide written informed consent.Biopsy proven adenocarcinoma of the rectum or sigmoid colon, or high-grade dysplasia with endoscopic or radiological features suggestive of cancer.Planned curative resection by high or low anterior resection.Suitable for elective open, laparoscopic or robotic surgery.American Society of Anesthesiologists grade ≤3.Able and willing to comply with trial procedures, including contraception requirements where applicable.

Presence of any of the following exclusion criteria will preclude participation in the trial:

Planned resection without anastomosis (eg, Hartmann’s procedure, abdominoperineal resection).Coexistent colorectal pathology (eg, inflammatory bowel disease).Contraindication to tranexamic acid (eg, known allergy, previous venous or arterial thrombosis, seizure disorder, disseminated intravascular coagulation, severe renal impairment).Pregnant, breastfeeding or likely to become pregnant within 3 months of surgery.

### Recruitment and consent

The timing of study procedures, clinical assessments and data collection points are summarised in online supplemental table 1. Potential participants will be identified through weekly colorectal multidisciplinary team meetings and systematic screening of surgical waiting lists. Those meeting the eligibility criteria will be approached by a member of the research team and provided with both verbal and written information about the study, including the participant information sheet.

Written informed consent will be obtained using the approved consent form by trial researchers trained in Good Clinical Practice. Consent will cover participation in the trial, administration of the allocated intervention, collection of clinical data and mandatory microbiome sampling. Separate consent will be sought for the optional qualitative substudy, typically during the participant’s attendance at the follow-up clinical appointment.

### Randomisation

Randomisation and allocation will be undertaken after confirmation of eligibility and completion of written informed consent. Allocation will be managed using a secure, 24-hour web-based randomisation service provided by Sealed Envelope.

Participants will be randomised in a 2:1 ratio to the tranexamic acid group or the control group. This allocation ratio was chosen to maximise knowledge of the intervention’s feasibility, safety and acceptability within a small sample size, while still exploring potential barriers to recruitment and randomisation, and benchmarking the control group’s experience and microbiome profile.

A minimisation algorithm with a random component will be applied to ensure balance across three prognostic factors known to influence anastomotic leak risk: sex (male; female), distance of the lower edge of the tumour from the anal verge (<8 cm; ≥8 cm) and receipt of neoadjuvant therapy (yes; no).

### Blinding

This trial will be conducted as an open-label study in which participants, the clinical team and the research team will be aware of the allocated intervention. An unblinded design was selected because the primary objectives are to assess feasibility, acceptability and safety of rectally administered tranexamic acid, with a particular focus on recruitment, compliance and practical barriers to delivery. As the study is not powered to evaluate treatment efficacy and does not involve subjective outcome measures, the absence of blinding is not anticipated to impact interpretation of any of the predefined progression criteria.

### Intervention

All participants will undergo anterior resection, according to the surgeon’s standard technique using an open, laparoscopic or robotic approach. At the end of the procedure, a rectal catheter will be inserted with the tip positioned just proximal to the anastomosis by the operating surgeon, allowing direct delivery of the allocated treatment to the anastomotic site.

Participants randomised to the intervention arm will receive tranexamic acid (1000 mg/50 mL) via the catheter immediately after creation of the anastomosis and once daily on postoperative days 1–3. Participants in the control arm will receive sterile water (50 mL) at the same time points. Sterile water is chosen as an inert comparator to replicate the administration procedure without introducing pharmacological effects, enabling assessment of feasibility, safety and acceptability while providing a baseline for mechanistic microbiome analyses.

The rectal catheter will be removed following administration of the final dose on postoperative day 3. If the rectal catheter becomes dislodged before all scheduled doses have been given, treatment will be discontinued, and treatment duration recorded.

### Safety monitoring

Adverse events will be considered for all participants from the signing of informed consent until 90 days after the last dose administration of investigational medicinal product. The active monitoring period for adverse events will be from the day of surgery until 24 hours following discontinuation of the study drug. Outside this period, investigators are still required to report any adverse events they become aware of.

Adverse events will be assessed for seriousness, causality and expectedness. All serious adverse events judged to be potentially related to the investigational medicinal product will be promptly reported to the University of Leeds as Sponsor (online supplemental file).

### Study outcomes and progression criteria

The primary outcome of this feasibility trial is to determine whether prespecified progression criteria are met to support progression to a phase III randomised controlled trial evaluating the clinical and cost-effectiveness of rectal tranexamic acid to prevent anastomotic leak.

Progression criteria address the key feasibility domains of recruitment, intervention adherence, retention and safety:

Recruitment: proportion of the target sample of 45 participants recruited.Intervention adherence: mean number of scheduled treatment doses received per participant.Retention: proportion of participants completing 90-day follow-up, including completeness of clinical outcome data and rates of withdrawal.Safety: adverse events, assessed for seriousness, causality and relatedness and summarised by type and incidence.

For recruitment, adherence and retention, quantitative thresholds will be applied using a stop-amend-go framework (table 1). ‘Stop’ outcomes indicate that progression to a definitive trial is not advisable unless modifiable barriers are identified and further feasibility testing is undertaken. ‘Amend’ outcomes indicate that modifications are required before proceeding to a larger study. ‘Go’ outcomes support progression to a definitive trial.

**Table 1 T1:** Progression criteria

Domain	Outcome measure	Stop	Amend	Go
Recruitment	Proportion of target sample (45 participants) recruited within 21 months.	<75% (<34 participants)	75–99% (34–44 participants)	100% (45 participants)
Adherence	Mean number of doses received per participant.	<50% (<2 doses on average)	50–74% (2–3 doses on average)	≥75% (≥3 doses on average)
Retention	Proportion of participants completing 90-day follow-up.	<70%	70–85%	>85%

Table 1 stop-amend-go thresholds for key feasibility domains. ‘Stop’ indicates that progression to a definitive trial is not advisable unless modifiable barriers are addressed and further feasibility testing is undertaken; ‘Amend’ indicates that modifications are required before proceeding to a larger study; ‘Go’ supports progression to a definitive trial. Safety will be considered separately through independent review of cumulative adverse event data by the Trial Oversight Committee (TOC) and will inform overall progression decision.

Safety is not included within the stop-amend-go framework because progression cannot be determined using numerical thresholds alone. The implications of adverse events depend on their frequency, severity, expectedness and causality. Accordingly, cumulative safety data, including that related to medicinal product and rectal catheter, will be reviewed by the independent TOC throughout the study and at study completion to determine whether any safety concerns preclude progression to a definitive phase III trial.

The decision to progress will be based on the overall assessment across all feasibility domains, informed by both quantitative thresholds and safety review. No single feasibility domain will determine progression in isolation. Where one or more domains fall within the ‘amend’ range, progression will be informed by consideration of the underlying reasons and whether these can be addressed through modifications to the trial design or conduct. In addition, insights from the mechanistic microbiome substudy and qualitative substudy will supplement this assessment by providing complementary biological and experiential perspectives on feasibility, acceptability and the potential treatment effect.

Clinical outcome data will also be collected to explore variability and inform the design of a potential future trial, including:

Anastomotic leak, defined and graded according to the International Study Group for Rectal Cancer criteria.^12^Postoperative complications assessed using the Clavien-Dindo classification.^13^

### Sample size

As a feasibility study, no formal power calculation has been performed. A total of 45 participants will be recruited, with 30 allocated to the tranexamic acid group and 15 to the control group. This sample size is sufficient to estimate feasibility outcomes, including recruitment, intervention adherence, retention and safety, to inform progression to a definitive trial.^14^

The 30 participants in the intervention group will also allow preliminary assessment of microbiome changes and associated bacterial collagenase activity, as well as collection of complication rates, providing mechanistic and clinical data to support the design of a potential future definitive trial.^14^

### Trial substudies

#### Microbiome substudy

All participants enrolled in the feasibility trial will also take part in a mandatory microbiome substudy, with consent obtained in parallel to the main trial. This substudy is designed to characterise changes in microbial composition and bacterial collagenase activity, providing mechanistic insight into treatment response.

Microbiome samples will be collected using rectal swabs from the rectal lumen at three time points: (1) preoperatively, (2) on the day of surgery and (3) on postoperative day 3–5.

Two exploratory analyses will be undertaken:

16S rRNA sequencing to determine how microbial populations change in response to tranexamic acid.Bacterial collagenase assay to quantify changes in collagenase production in response to tranexamic acid.^15^

#### Qualitative substudy

An optional qualitative substudy will be conducted to explore the acceptability of both the intervention and trial processes.

A maximum variation sampling approach will be used to ensure diversity of views by age, sex and treatment arm. Up to 15 trial participants will be interviewed (10 participants from the tranexamic acid group, and 5 participants from the control group), alongside 5 individuals who declined participation in the main trial to capture reasons for non-participation. In addition, five surgeons or healthcare professionals will be interviewed to provide their experiences of the intervention for patients under their care.

Semi-structured interviews, guided by pre-designed topic guides, will be conducted by a study investigator trained in qualitative research methods in hospital or outpatient settings and will last approximately 30–45 min. Interviews will be audio-recorded, transcribed verbatim and thematically analysed to identify key factors influencing trial feasibility and acceptability.^16^

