## Discussion

This protocol describes a feasibility trial of rectally administered tranexamic acid to prevent anastomotic leak after anterior resection for rectal and sigmoid cancer. The study combines translational microbiome science with surgical innovation, exploring whether a widely used, established drug can be repurposed and delivered locally to modify a microbiome-mediated pathway implicated in anastomotic leak.

Tranexamic acid has been used safely for decades in surgical practice, most commonly given intravenously or orally to prevent and treat bleeding. Reported adverse events are generally mild, and serious complications are rare. In this trial, rectal administration represents an off-label route, designed to achieve high local concentrations at the anastomotic site while limiting systemic absorption. Pharmacokinetic studies of topical and rectal administration have demonstrated very low serum concentrations after local delivery—well below the threshold required to impair systemic fibrinolysis—providing reassurance that the risk of systemic side effects is minimal.^20
21^

Delivery will be facilitated by a rectal catheter, enabling precise administration of tranexamic acid into the bowel lumen at the site of the anastomosis. Rectal catheters are widely used following anterior resection and have a reassuring safety profile, including potential reductions in anastomotic leak through lowered endoluminal pressure and temporary faecal diversion.^22^ The novel aspect of this study is the use of the catheter to deliver a therapeutic agent to the anastomosis, for which there is limited precedent. A single-centre study demonstrated that repeated administration of an antibiotic solution via rectal catheter after rectal cancer surgery was feasible and safe, with no intervention-related adverse events.^23^ These findings are encouraging, but they do not remove uncertainty: questions remain around catheter retention, tolerance and acceptability, and addressing these practical issues is a central objective of this feasibility trial.

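### Patient interviewees are chosen by age, sex and arm and usually consented at the follow-up clinic, so nothing ensures that those who stopped dosing early or withdrew are heard (minor)

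*Protocol article*

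**What the plan says.** The Qualitative substudy section gives the purpose: "An optional qualitative substudy will be conducted to explore the acceptability of both the intervention and trial processes". It then fixes how trial participants are chosen: "A maximum variation sampling approach will be used to ensure diversity of views by age, sex and treatment arm". The numbers are: "Up to 15 trial participants will be interviewed (10 participants from the tranexamic acid group, and 5 participants from the control group"). Two further groups are interviewed: "alongside 5 individuals who declined participation in the main trial to capture reasons for non-participation", and "five surgeons or healthcare professionals will be interviewed to provide their experiences of the intervention for patients under their care".

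The consent point is in the Recruitment and consent section: "Separate consent will be sought for the optional qualitative substudy, typically during the participant’s attendance at the follow-up clinical appointment".

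The Intervention section foresees early stopping: "If the rectal catheter becomes dislodged before all scheduled doses have been given, treatment will be discontinued, and treatment duration recorded". The Study design section follows every participant for 90 days, and the progression criteria count withdrawals under retention. The Discussion says that "questions remain around catheter retention, tolerance and acceptability, and addressing these practical issues is a central objective of this feasibility trial". The Study outcomes and progression criteria section has the qualitative findings supplement the overall progression assessment.

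**The concern.** Acceptability is part of the stated aim, and the interviews are the component assigned to explore it. Maximum variation sampling works by varying the characteristics most likely to shape the experience under study. Here a likely one is whether the participant received all four doses, stopped early or left the trial, and it is not among the three listed dimensions. The consent point adds a second filter, because someone who has withdrawn or does not come to clinic is not met by the usual approach.

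The other interviewees do not fill the gap. People who declined the trial never had the study intervention, and professionals can describe a patient's tolerance only at second hand. Dose counts and withdrawal rates show how many stopped, not what the experience was like. If the patient interviews lean towards completers, the phase III decision is supplemented by a more favourable picture of acceptability than the whole group would give.

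**Working it through.** The document gives no figure for interview coverage, so there is none to reproduce. As a consistency check, 45 at 2:1 gives 30 and 15, and the interview split of 10 and 5 keeps the same ratio.

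**Step 1: separate the two groups.**
- *Withdrawn participants and non-attenders.* The usual consent approach takes place at an appointment they do not attend. The article describes no other route for them, but the word *typically* leaves one open.
- *Early stoppers who stay in the trial.* Dislodgement ends dosing, not follow-up. They can attend clinic and be asked. They are missed only if the selection happens not to include them.

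**Step 2: illustrate the second group.** Inputs from the document: 30 participants on tranexamic acid, 10 of them interviewed. Assumptions not in the document: k of the 30 stop early, all 30 can be approached, and selection is unrelated to stopping. Then

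P(no stopper interviewed) = C(30−k, 10) / C(30, 10)

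P(at most one) = [C(30−k, 10) + k·C(30−k, 9)] / C(30, 10)

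Expected number interviewed = 10k/30

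For k = 3, the first formula reduces to (20×19×18)/(30×29×28) = 6840/24360 = 0.281.

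| k (assumed) | P(none) | P(at most one) | Expected |
|---|---|---|---|
| 3 | 28.1% | 74.9% | 1.0 |
| 6 | 6.5% | 32.6% | 2.0 |
| 10 | 0.6% | 6.2% | 3.3 |
| 11 | 0.3% | 3.7% | 3.7 |

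**Step 3: relate k to the adherence bands in Table 1.**
- The Go band needs a mean of at least 3 of 4 doses. In the tranexamic acid arm it can be met with 10 participants receiving one dose each: (20×4 + 10×1)/30 = 3.0.
- A mean below 3 in that arm means fewer than 90 of 120 doses given, so at least 31 missed. If everyone receives the intraoperative dose, each can miss at most 3, and 31/3 = 10.3, so at least 11 stopped early. For k = 11, P(none) = C(19,10)/C(30,10) = 92,378/30,045,015 = 0.3%.

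The chance of hearing from no early stopper is therefore material only when stopping is uncommon. When stopping is frequent enough to put adherence below Go in that arm, some stoppers would almost certainly be interviewed, provided they stay reachable.

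**The case against.** The strongest reply is that the design leaves more room than a quick reading suggests. Consent is *typically*, not always, sought at the clinic. Interviews may be held in hospital as well as in outpatients, and decliners are recruited without any trial follow-up. The interviews are optional and exploratory, and are one input beside adherence, retention and safety review. The professionals may have cared for patients who stopped. The article condenses a fuller protocol that may contain a more detailed sampling frame. All of this stands and limits the weight of the point. It does not change the fact that the article lists three dimensions and completion status is not one of them.

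A reader might also infer more than the document supports:
- *That the consent point excludes early stoppers.* It does not, since they remain in 90-day follow-up.
- *That up to 6 of 45 participants would never be asked, because retention can still be Go at 39/45 = 86.7%.* Retention is measured at 90 days and the article does not date the clinic appointment. Someone lost by day 90 may already have been approached.
- *That acceptability will be biased favourably and the reasons for stopping left unexplored.* This is a possibility, not a demonstrated result, and Step 3 shows it is unlikely for early stoppers when adherence in the tranexamic acid arm falls below Go.
- *That the interviews are the designated explanation of an Amend result.* The article calls for the underlying reasons to be considered, and says separately that the qualitative findings supplement the assessment.

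The percentages also treat a purposive sample as if it were random, so they illustrate and do not predict.

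**Conclusion.** The point holds as a minor item. The stated sampling dimensions and usual consent point can under-represent participants who stopped dosing early, withdrew or did not attend, and these are informative about whether the catheter is tolerated. For those who withdraw or do not attend, the weakness is the consent route. For early stoppers who remain in follow-up, it is only that inclusion is left to chance.

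The size of any bias cannot be derived from the document. The illustrative chance of interviewing no early stopper runs from about 28% (3 of 30) through about 7% (6 of 30) to under 1% (11 or more). It rests on assumed stopping counts and on selection that ignores stopping. The last figure also assumes that every participant in that arm receives the intraoperative dose.

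**What to change.** In the Qualitative substudy section, add treatment and trial completion status as a fourth sampling dimension, with the categories all doses received, stopped early, and withdrew from the trial. Keep the total at 15 trial participants. Treatment duration is already to be recorded after dislodgement and withdrawals are already counted, so little new data collection should be needed.

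In the Recruitment and consent section, seek optional consent to be contacted for interview at the main consent. Reconfirm it when treatment stops or the participant withdraws, leaving the participant free to decline.

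The cost is a small amendment to the consent form and slightly fewer interviews with completers. Some early consents to contact will go unused. No additional interviews are needed.
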